***Table 5:* *Expected control group means, SDs, and differences detectable (alpha= 0.05, 80% Power)***

| **Continuous Outcomes** | **Mean** | **SD** | **Mean detectable differences: ITT** | **Breastfeeding effect to produce detectable effect** | **Differences observed in other studies** |
| --- | --- | --- | --- | --- | --- |
| Global cognitive score | 100 | 15 | 1.5 | 4.1 | 2-5^16^ |
| FEV_1_ (mls)^a^ | 3345 | 480 | 48 | 130 | 40^59^ |
| FVC (mls)^a^ | 3700 | 575 | 58 | 150 | 54-103^58,59^ |
| PEFR (mls/s)^a^ | 6200 | 800 | 80 | 200 | 180^4,59^ |
| LogMar visual acuity | 0.02^b^ | 0.2^b^ | 0.02 | 0.05 | 0.05^5-7,101,158^ |
| Systolic blood pressure (mmHg)^159^ | 99.9 | 9.6 | 1.15 | 3.11 | Meta-analysis: 1.4 Max difference: 6.5^160^ |
| Diastolic blood pressure (mmHg)^159^ | 57.0 | 6.8 | 0.82 | 2.22 | Meta-analysis: 0.5; Max differences: 3.4^161,162^ |
| Body mass index (kg/m^2^) ^c^ | 16.2 | 2.0 | 0.024 | 0.06 | 0.4^163^; 0.28-0.57^72,164^ |

^a^Data from ALSPAC, standardized for height; ^b^Northern Ireland Childhood Errors of Refraction study (personal communication); ^c^Estimates of means and SDs obtained from ALSPAC.

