**f. Outcomes at age 11 years (PROBIT III)**

***Table 4: Intra-class correlation coefficients (ICC) for measurements taken in PROBIT III***

| *Measurement* | *ICC* |
| --- | --- |
| Standing height | 0.03 |
| Sitting height | 0.03 |
| Weight | 0.02 |
| Bioimpedance | 0.01 |
| Mid-upper arm circumference | 0.03 |
| Systolic blood pressure | 0.12 |
| Waist circumference | 0.07 |
| Hip circumference | 0.03 |
| Head circumference | 0.10 |
| Triceps skinfold thickness | 0.12 |
| Subscapular skinfold thickness | 0.04 |
| Glucose | 0.08 |

At 11.5 years (PROBIT III), we investigated effects of breastfeeding on growth and cardio-metabolic risk factors. Pediatricians performed anthropometric measurements on mothers and children, and collected fasting blood via fingerstick. We have completed all study visits and await final data entry and results of laboratory assays. The participation rate - 13,891 children were seen – attests to our ability to maintain excellent follow-up and thus minimize retention bias. Intra-class correlation coefficients were extremely low for all measured outcomes (**Table 4**), indicating valid measurements with a low degree of clustering.

In an interim intention-to-treat analysis (n = 12,374), cluster-adjusted mean differences in experimental vs. control groups were essentially null: 0.16kg/m^2^ (95% CI: -0.08, 0.40) for BMI; 0.43% (-0.15, 1.01) for body fat; 0.33cm (-1.25, 1.92) for waist circumference; 0.11mm (-1.53, 1.74) for triceps skinfold thickness; 0.62cm (-0.40, 1.64) for height; and 1.12mmHg (-1.06, 3.30) for systolic blood pressure.^141^ The odds ratio for obesity (experimental vs. control arms) was 1.19 (0.95, 1.50). We found similar null results for maternal postpartum adiposity.^142^ We now have a number of papers in progress presenting results of the intention-to-treat analysis of the anthropometric and biochemical study outcomes. Our joint experience leading PROBIT III yields several important messages: we have demonstrated our successful collaboration in leading a PROBIT outcome visit; we achieved high rates of follow-up with little evidence for bias in follow-up or clustering in outcome assessments; and we require 4 years of funding to allow for complete data collection and analysis.

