**2.3.6. Power**

Based on follow-up in PROBIT I-III, we expect 14,000 participants in PROBIT IV. We calculated detectable differences based on this number of subjects in 31 clusters, an intention-to-treat (ITT) analysis, 80% power, 5% significance, and used a realistic value (0.01) of the intra-cluster correlation coefficient (ICC) based on the ICCs of outcomes in PROBIT I-III. The effective sample size in PROBIT IV, allowing for the clustered design, is the total number of anticipated participants (14,000) divided by the design effect (*Deff*), where *Deff* = 1+(*n*-1)×ICC and *n* is the average number of individuals per cluster (n=14,000/31=451).^156^ Thus, the design effect for an ICC of 0.01 is 1+4.5=5.5 and the effective sample size is 2,500 children (14,000/5.5). Expected means and SDs for each outcome were taken from childhood cohorts of similar age. Mean detectable differences, assuming exposure groups are dichotomized at the midpoint, are calculated as the product of the SD of each variable and the standardized difference (i.e. 0.1 given an effective sample size of 2,500^157^). For the categorical atopic eczema outcome at the 16-year follow-up (flexural eczema on skin examination), the study has 94% power at the 5% significance level to detect a 50% reduction in atopic eczema prevalence between the two study groups, similar to PROBIT I.^21^

**Table 5** shows the mean differences that can be detected in the comparison of the two randomized arms by ITT and the corresponding effect due to breastfeeding that would have to be present to achieve those ITT differences. The breastfeeding effect is based on the difference in exclusive breastfeeding at 3 months of 43% in the intervention arm and 6% among controls, and is derived by dividing the ITT differences by 0.37=37% (the difference in exclusive breastfeeding in the 2 arms). For comparison, published differences are shown. The sample size is adequate for detecting important differences in the outcomes (**Table 5**). If we fail to find associations in the ITT analysis, the study is powered to have narrow confidence intervals (CIs) around null estimates. The 95% CIs for zero mean differences, assuming an effective sample size of 1250 in each arm ((14,000/Deff) ÷ 2) and means/SDs in Table 2, would be: cognitive score ± 1.2; FEV_1_ ± 40mls; FVC: ± 45mls; PEFR: ± 60mls/s.

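### In Table 5 the BMI detectable differences (0.024 and 0.06 kg/m²) do not follow from the protocol's own rule and are about 8 to 10 times too small

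*Protocol*

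**What the plan says.** Section 2.3.6 sets out the calculation. The targets are "80% power, 5% significance". The team writes "we expect 14,000 participants in PROBIT IV" and "used a realistic value (0.01) of the intra-cluster correlation coefficient (ICC"). The cluster size "is the average number of individuals per cluster (n=14,000/31=451"), and the design effect is "1+4.5=5.5 and the effective sample size is 2,500 children (14,000/5.5"). Detectable differences are "calculated as the product of the SD of each variable and the standardized difference", which the same sentence puts at 0.1. The breastfeeding effect is the ITT difference divided by 0.37, the gap between arms in exclusive breastfeeding at 3 months.

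Table 5 applies this to eight outcomes. Its BMI row, "16.2 | 2.0 | 0.024 | 0.06 | 0.4", gives a mean of 16.2, an SD of 2.0, an ITT difference of 0.024 and a breastfeeding effect of 0.06. Beside them stand published differences of 0.4 and 0.28 to 0.57. The text then refers to Table 5 in calling the sample size adequate for important differences in the outcomes. Section 2.3.3 f reports the trial's own interim BMI result at 11.5 years: "0.16kg/m^2^ (95% CI: -0.08, 0.40) for BMI".

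**The concern.** The ratio of 0.024 to the SD of 2.0 is 0.012, whereas the rule calls for 0.1. Nothing in the text gives BMI a smaller multiplier. Damage in reading the table is unlikely, because the two cells agree with each other: 0.024/0.37 = 0.065, printed as 0.06.

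Adiposity is part of Aim 3, and BMI is the only adiposity row in Table 5. The wrong cells are therefore the protocol's only statement of power for adiposity. A reader would conclude that the trial can detect BMI effects far smaller than any it cites, and would take a null BMI result as excluding much more than it can.

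**Working it through.** **Inputs (section 2.3.6 and Table 5).** Effective sample size 2,500, so 1,250 per arm; alpha 0.05, taken as two-sided because the text does not say; power 80%; BMI SD 2.0; divisor 0.37.

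**1. The design effect reproduces.** 14,000/31 = 451.6 per cluster; 1 + 450.6 × 0.01 = 5.51; 14,000/5.51 is about 2,540, which the protocol rounds to 2,500.

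**2. The standard error formula reproduces the protocol's own intervals.** SE = SD × √(2/1,250) = SD × 0.04. For cognition, 1.96 × 15 × 0.04 = 1.18 (printed ± 1.2). For FVC, 1.96 × 575 × 0.04 = 45 (printed ± 45). For BMI, SE = 0.08 and the corresponding half-width would be 0.16, already more than six times 0.024.

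**3. Multiplier in each row (ITT difference / SD).**

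| Outcome | SD | ITT difference | Ratio |
| --- | --- | --- | --- |
| Cognition | 15 | 1.5 | 0.100 |
| FEV1 | 480 | 48 | 0.100 |
| FVC | 575 | 58 | 0.101 |
| PEFR | 800 | 80 | 0.100 |
| LogMAR | 0.2 | 0.02 | 0.100 |
| Systolic BP | 9.6 | 1.15 | 0.120 |
| Diastolic BP | 6.8 | 0.82 | 0.121 |
| BMI | 2.0 | 0.024 | **0.012** |

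**4. Corrected BMI values.**

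| Basis | ITT difference | Divided by 0.37 | Ratio to 0.024 |
| --- | --- | --- | --- |
| Stated rule, 0.1 × 2.0 | 0.20 | 0.54 | 8.3 |
| Exact, 2.80 × 0.08 | 0.224 | 0.61 | 9.3 |
| Blood pressure multiplier, 0.12 × 2.0 | 0.24 | 0.65 | 10 |

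**5. Power at the printed value.** 0.024/0.08 = 0.30. Power = Φ(0.30 − 1.96) + Φ(−0.30 − 1.96) = 0.048 + 0.012 = 0.060.

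**6. Other readings that might give 0.024.** One-sided alpha: (1.645 + 0.842) × 0.08 = 0.20. No clustering, 7,000 per arm: 2.80 × 2.0 × √(2/7,000) = 0.095. No clustering and one-sided: 0.084. None comes close. Reaching 0.024 at 80% power needs 2 × (2.80 × 2.0/0.024)², about 109,000 effective children per arm.

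**7. Against the published differences.** Breastfeeding effects of 0.28, 0.40 and 0.57 become ITT differences of 0.104, 0.148 and 0.211 after multiplying by 0.37. With SE 0.08, power is about 25%, 46% and 75%.

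**8. Cross-check on the trial's own data.** The 11.5-year interim interval runs from −0.08 to 0.40, a half-width of 0.24. That is ten times the difference printed as detectable, from 12,374 children.

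**The case against.** The printed cells cannot be defended, but several stronger conclusions that a reader might draw go too far.

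- **That the slip is exactly ten-fold.** This holds only with the 0.12 multiplier, which is inferred from the blood pressure rows. By the stated rule the factor is 8.3.
- **That adequacy reverses for BMI, so BMI should be struck from the adequate outcomes.** The adequacy sentence is general and does not name BMI. Other, correctly scaled rows also need effects above their comparators: FEV1 130 against 40, FVC 150 against 54 to 103, PEFR 200 against 180, and systolic and diastolic pressure 3.11 and 2.22 against meta-analysis values of 1.4 and 0.5. A corrected BMI row joins that pattern. Under the stated rule its 0.54 also lies just inside 0.28 to 0.57. The documents do not show that the cited studies' contrasts match exclusive breastfeeding at 3 months, so the comparison is approximate.
- **That the interim interval should supply the new values.** Its SE is 0.48/3.92 = 0.122, giving 2.80 × 0.122 = 0.34 for ITT and 0.93 after division by 0.37. Those figures describe precision at 11.5 years with 12,374 children, whereas Table 5 is defined for 14,000 children, an ICC of 0.01 and external SDs. The interval shows that 0.024 is out of reach; it does not replace the calculation.
- **That the design is at fault.** Follow-up is sought for everyone enrolled in a closed cohort, so no sample size decision rests on this cell. BMI is also one of several Aim 3 outcomes.

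All four limits stand. They narrow the consequence but leave the error in place: the table states a difference detectable at 80% power that the design cannot detect.

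**Conclusion.** The two BMI cells are wrong as written. On the protocol's own inputs (SD 2.0, effective sample size 2,500, two-sided 5%, 80% power, divisor 0.37) they should be 0.20 to 0.24 for the ITT difference and 0.54 to 0.65 for the breastfeeding effect, depending on the multiplier. The required breastfeeding effect then exceeds the published 0.4 and is near or above the top of 0.28 to 0.57.

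These sizes depend on the stated SD and ICC. Table 4 has no ICC for BMI. At 0.02, the value it lists for weight, the figures would be about 0.30 and 0.81, so the stated ICC is not the pessimistic case.

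The harm is confined to the power statement for BMI and to how a null BMI result would be read.

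**What to change.** Recompute both BMI cells with one multiplier, state it in section 2.3.6, and use it in every row of Table 5. If the stated 0.1 is kept, BMI becomes 0.20 and 0.54, and the blood pressure rows come down from 0.12 to match. In that case note that 0.1 is rounded: at 1,250 per arm, 0.1 SD has Φ(2.5 − 1.96), about 71% power. If the table is to match its 80% label, use 0.112 throughout, which gives 0.22 and 0.61 for BMI.

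Then qualify the adequacy sentence for BMI, for example by stating that the required breastfeeding effect is above 0.4 and near or above the top of the published range.

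The correction itself costs two cells and one sentence, plus small changes in other rows to make the multiplier uniform. The stated power for BMI becomes less favourable. Recruitment, data collection and the analysis are unchanged.

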**2.3.7. Timeline**

As summarized in **Figure 2**, we anticipate completing all proposed work during the 4 year duration of the project. During the first 6 months we will finalize the training materials, DVD’s, and manual of procedures. We will hold our initial training workshop midway through Year 1, after which the pediatricians will commence data collection. Monitoring visits will begin a few months after the first visits are conducted. Based on experience in PROBIT III, we anticipate all 14,000 children will be seen over 2.5 years, after which we will complete the audit visits, data analysis, and manuscript writing. Although the NIH grant supporting PROBIT III operations was a 3-year grant, we required a fourth no-cost-extension year to complete data collection and analysis. Thus, we believe that 4 years is a reasonable timeline for the proposed work.

***Figure 2: Project Timeline***

**2.3.8. Strengths and limitations**.

***Significance.*** This study is significant because it will yield results that can directly influence breastfeeding promotion policies and thereby influence child health.

***Approach.*** Our proposal combines the strength of a randomized design, minimizing confounding, and high rates of follow-up, minimizing selection bias. This project thus offers a unique opportunity to determine the long-term effect of a breastfeeding promotion intervention on child neurocognitive and lung function, adiposity and blood pressure. In the PROBIT trial, we successfully randomized units of medical care (hospitals and affiliated outpatient clinics) to breastfeeding promotion or usual care, resulting in large contrasts in breastfeeding experience between the two groups. In contrast to observational epidemiologic studies, in which residual confounding remains a concern even after adjustment for identified confounders, this intention-to-treat analysis will provide un-confounded estimates of the influence of breastfeeding on maternal adiposity. Breastfeeding was ascertained at regular intervals during infancy, with definitions of exclusive breastfeeding based on strict WHO criteria,^165^ minimizing measurement error. Modern alternatives to breastfeeding form the reference exposure, providing results of contemporary relevance.

The large sample size limits potential type 2 error for effect sizes of clinical and public health importance. We already have strong evidence supporting the internal validity of the conduct of the study, which would not be guaranteed if a study were established *de novo*. The stringent random allocation procedure produced intervention and control groups with similar baseline characteristics.^21^ Measurement error will be minimized by the use of standard, calibrated equipment. Pediatricians will be rigorously trained and retrained to obtain valid, reproducible measurements. Data monitoring and the extremely low intra-class correlations in previous phases of PROBIT (**Table 4**) support the precision of the outcome data collected to date.

We will minimize potential bias in outcome assessment by using self-administered, computer-scored measures of cognitive function. Although the polyclinic pediatricians cannot not be blinded to the intervention or control status, the pattern of results in previous phases of PROBIT follow-up (i.e. no effect seen for respiratory infections in infancy or child adiposity^21,23^), do not suggest systematic bias towards better outcomes in the intervention group. The duplicate audit visits will provide additional evidence against bias due to non-blinding. Losses to follow up and incomplete data are potential sources of bias. We expect similar high rates of follow-up as we achieved in PROBIT III. We will be able to compare and account for characteristics at baseline and at earlier follow-up visits between children who do and do not present for assessment at age 15-16. Compared with observational cohorts, registered trials are less prone to problems of selective submission and publication bias. Generalizability is a concern. As the study is in Belarus, all participants are white. However, PROBIT includes an economically diverse population, and fewer than 2% of eligible mothers refused initial participation in the study. Belarus resembles Western developed countries in both basic health services and sanitary conditions. An uncontaminated water supply is ensured and monitored throughout the Republic by public health authorities, and clinics and physicians are abundant and readily accessible, even in rural areas. Therefore, we believe it will be reasonable to generalize results to children in the US.

This proposal represents good value. Previous grants have already supported recruitment, collection of baseline characteristics, and delivery of the intervention. As detailed in the budgets, the Canadian Institutes of Health Research will provide substantial co-funding (~$1.2m). We require funding only for the collection and analysis of outcome measures. In addition to the proposed aims, great potential exists for the conduct of other epidemiologic research based on earlier follow-ups and stored blood, including genetic analyses.

***Innovation.*** This study will fill a crucial gap in the literature linking breastfeeding with important health outcomes in adolescence. Most previous studies have been observational. Additional limitations of the available literature include short duration of follow-up, recalled breastfeeding history, and assessment of asthma outcomes via questionnaire rather than objective measures such as spirometry. We will determine the causal effects of breastfeeding in the largest RCT in the field of human lactation ever, and by adding these 3 outcomes will complete analyses on a large range of outcomes over the 4 phases of PROBIT.

***Investigators and environment.*** We have assembled an outstanding team of investigators with appropriate expertise and proven collaboration and productivity. We build upon an innovative cluster randomized controlled trial that successfully increased breastfeeding duration and exclusivity. The high quality of data collection is established. The environments will provide strong support to ensure the success of the study.

# Trial Registration isrctn.org: ISRCTN37687716:

ISRCTN37687716 DOI 10.1186/ISRCTN37687716

PROmotion of Breastfeeding Intervention

Trial

Condition category

Pregnancy and Childbirth

Date applied

25/02/2005

Date assigned

09/09/2005

Last edited

13/02/2015

Prospective/Retrospective Retrospectively registered

Overall trial status Completed

Recruitment status No longer recruiting

# Plain English Summary

Background and study aims

The Promotion of Breastfeeding Intervention Trial (PROBIT) is a study in the Republic of Belarus involving 31 maternity hospitals and affiliated clinics across the country. The study was designed to help scientists, health care providers, and the general public understand the effects of infant feeding on child health and development.

In 1995, 16 hospitals and clinics were randomly allocated to a breastfeeding promotion intervention based on World Health Organization materials and procedures, while 15 continued breastfeeding practices in place at the time of random allocation. Mothers and babies were recruited from June 1996 to December 1997. In total, 17,046 mothers and their babies were recruited into the study. Of these, 16,492 (97%) were followed at regular intervals until the infants were 12 months of age. Detailed information was recorded at each followup visit about infant feeding, digestive and lung infections, and rashes.

When PROBIT children were six and a half years old, 13,889 (81%) were examined for height, weight, body fat, blood pressure, behaviour, dental health, intelligence quotient (IQ), asthma and allergy. At age 11 and a half years, 13,879 (81%) were again examined for height, weight, body fat, blood pressure, and also had blood tests to measure diabetes and heart disease risk factors. Currently we are seeing the children at age 16 years.

Who can participate?

Recruitment is complete. Mothers and their babies joined the study during their delivery hospital stay. Mothers could take part if they started breastfeeding, and they and their baby were healthy.

What does the study involve?

At the current visit, when the child is 16, the pediatrician:

1. Measures the child’s height, waist, blood pressure, weight and body fat.
2. Tests the child's vision by asking him/her to read letter charts. A small number of children are also testedusing an instrument that assesses whether they need glasses. 3. Examines the child’s skin for rashes.
3. Tests the child’s lung health by asking him or her to blow into a tube three to eight times to measure the capacity of the lungs.
4. Asks the child to take a computer­administered test of brain development (including memory, ability tosolve problems, attention, perception, verbal skills, information processing and motor skills).
5. Administers a questionnaire to assess other aspects of the child’s health and physical development.

What are the possible benefits and risks of participating?

The lung function assessment involves blowing hard into a tube several times. Repeated blowing may cause some people to become wheezy. The pediatrician has asthma medication on hand to relieve these symptoms if they occur. None of the other measures or tests carries any risk to the child. As a result of the examination, the pediatrician may identify previously undiagnosed eye, lung or blood pressure problems in the child, which will then be followed up appropriately.

Where is the study run from?

The study is run from the The National Research and Applied Medicine Mother and Child Centre (Minsk,

Belarus), in collaboration with the School of Social and Community Medicine, University of Bristol (Bristol,

UK), Departments of Pediatrics and of Epidemiology, Biostatistics and Occupational Health, McGill

University Faculty of Medicine (Montreal, Canada), and Harvard Medical School and Harvard Pilgrim

Health Care Institute (Boston, USA).

When is the study starting and how long is it expected to run for?

The study started in January 1995 and is expected to run until December 2015. We hope the study will extend beyond this time as we intend to look at the children’s health over many years.

Who is funding the study?

This study is supported by a grant from the Canadian Institutes of Health Research (CIHR) and the US National Institutes of Health (NIH). The study has previously been funded by the National Health Research and Development Program (NHRDP) Health Canada, European Union’s project on Early Nutrition

Programming: Long­term Efficacy and Safety Trials, the Thrasher Research Fund (USA), the United Nations Children’s Fund (UNICEF), and the European Regional Office of the World Health Organization (WHO).

Who is the main contact?

[name] [name]

[contact] Trial website

http://www.bristol.ac.uk/social­community­medicine/projects/probit/ [http://www.bristol.ac.uk/socialcommunity­medicine/projects/probit/]

